## Abstract

**Background::**

Acute pancreatitis (AP) usually has a mild course with a mortality rate below 1%. However, around 10% of patients develop severe AP (SAP) involving extra-pancreatic tissues and other organ systems. The mortality of SAP is around 42%. The outcome of SAP is closely related to the development of systemic inflammation and consecutive organ failures. Most current therapies including fluid resuscitation, antimicrobial therapy, drainage procedures, and endoscopic management of complications are symptomatic rather than causative approaches, except sphincterotomy for gallstone pancreatitis. Regarding the high mortality of SAP and its close association with systemic inflammation, extracorporeal removal of inflammatory mediators is an appealing approach. Several recent studies have demonstrated that the CytoSorb adsorber effectively eliminates inflammatory cytokines, such as IL-1ß, IL-6, IL-8, IL-10, and TNF-alpha. Some of these trials suggested that therapy with CytoSorb might improve outcome, including a reduction in the vasopressor dosage and reversal of shock.

Therefore, it is the objective of this study to evaluate the effectiveness of 2 consecutive 24 h-treatments with CytoSorb on hemodynamics in patients with early SAP.

**Methods::**

This study includes patients with early SAP (APACHE-II ≥10) and transpulmonary thermodilution hemodynamic monitoring (PiCCO; EV-1000) within a maximum of seven days from the onset of pain. Eligible patients will be treated with 2 consecutive periods of CytoSorb. A 20%-improvement in the vasopressor dependency index (VDI) - which relates is derived from mean arterial pressure (MAP) and catecholamine dosage - is the primary outcome. In addition to this clinical outcome, there are several laboratory (cytokine levels) and translational endpoints (including multiplex-ELISAs of numerous anti- and pro-inflammatory cytokines/chemokines and DNA analyses). Primary outcome analysis will compare the incidence of the primary endpoint in 30 patients from the intervention group to 60 matched controls with advanced hemodynamic monitoring recruited from recent studies in SAP within the same setting and the same centers.

**Discussion::**

A potential improvement in hemodynamics and/or other outcomes by CytoSorb would provide a new therapeutic option in the early treatment of SAP with a pathophysiological rationale.

**Trial registration::**

This study was registered on March 17, 2017 (ClinicalTrials.gov Identifier: NCT03082469). URL: https://clinicaltrials.gov/ct2/show/NCT03082469.

**Version::**

V_PACIFIC_1.0 September 30, 2018.

## Background

1

Acute pancreatitis (AP) is an acute inflammatory process of the pancreas.^[1–4]^ In about 90% of patients, AP has a mild course with inflammation localized to the pancreatic gland. Mild AP has a mortality rate below 1%.^[1]^ The remaining 10% of patients develop severe AP (SAP) involving extra-pancreatic tissues and other organ systems. The outcome of SAP is closely related to the development of systemic inflammatory response syndrome (SIRS) and consecutive multiple organ failures (MOF). The mortality of SAP is around 42%.^[5]^

*Diagnosis* of AP is easily established based on the presence of at least 2 of the 3 criteria of typical epigastric pain with radiation to the back, at least 3-fold elevation of serum lipase or amylase, and evidence of AP on abdominal ultrasound or computed tomography (CT). By contrast, *therapy* for SAP is cumbersome and limited due to the lack of causative therapies apart from the removal of bile duct stones. Consequently, the therapy for SAP is predominantly symptomatic. Optimized fluid resuscitation is the cornerstone of these symptomatic therapeutic approaches, since early volume depletion and hemo-concentration have been repeatedly associated with poor outcome. In addition, early goal-directed resuscitation based on transpulmonary thermodilution (TPTD) might potentially improve outcome in SAP.^[4,6,7]^

Severity and mortality of AP are 2-peaked, with an early peak due to overwhelming SIRS and a second peak after 2 to 4 weeks, predominantly due to septic complications. With regard to the marked inflammatory response (“cytokine storm”) several attempts to prevent or limit inflammation have been investigated. However, none of the medical concepts including antioxidants,^[8]^ platelet-activating antagonists,^[9]^ antibodies against mediators of inflammation such as tumor necrosis factor alpha, or non-steroidal anti-inflammatory drugs have been shown to improve outcome in large clinical trials. This might be related to the protracted intervention aimed at limiting SIRS in a fulminant disease with already established “cytokine storm”. In addition to the delayed onset of action of medical immune-modulators, these drugs also carry the risk of side-effects, and may further impair organ function.

In this scenario, blood-purification with hemofiltration and/or hemo-adsorption with immediate elimination of cytokines may be a promising alternative.^[10]^

Several recent studies have investigated the CytoSorb (CytoSorbents Corporation, Monmouth Junction, NJ) cytokine adsorber.^[10–12]^ CytoSorb is a biocompatible adsorber approved for use in patients with elevated inflammatory mediators, with absorption rates for inflammatory cytokines, such as IL-1ß, IL-6, IL-8, IL-10, and TNF-alpha.^[11,13]^ Several studies, predominantly in septic patients, suggest that effective elimination of these mediators may be associated with improved outcome, including reduction in the vasopressor dosage and reversal of shock.^[11]^

### Aim, design and setting of the study

1.1

It is the objective of the PACIFIC-study to investigate if early administration of CytoSorb in patients with SAP substantially improves hemodynamic characteristics including vasopressor dosage and cardiac power index (CPI).

The PACIFIC-trial is designed as a prospective multi-center case-control study.

The study will be performed in intensive care units (ICU) experienced in the use of CytoSorb and capable of combined TPTD and pulse contour analysis (PCA) monitoring.

All patients will be monitored by PiCCO (Pulsion Medical systems SA, Feldkirchen, Germany) or EV-1000 (Edwards Lifesciences, Irvine, CA).

The matched controls will be recruited from patients with SAP treated in a comparable setting including TPTD-monitoring, but not treatment with CytoSorb or any other cytokine adsorbing devices.

### Characteristics of participants and description of materials

1.2

#### Inclusion and exclusion criteria

1.2.1

Patients with SAP and an APACHE-II-score ≥10 are eligible for 7 days after the onset of pain. The main inclusion criteria (see Table 1) are:

proven AP;within 7 days of the onset of pain;in combination with criteria associated with increased severity and poor outcome of AP.

**Table 1 T1:**
[figure not shown]
Inclusion criteria.

Inclusion is limited to a maximum of 7 days after the onset of pain. This period is considered as the early phase of SAP, including the first peak of inflammation due to a SIRS.

Patients can only be included if they are under hemodynamic monitoring with TPTD irrespective of the study.

With regard to the representativeness of the data, exclusion criteria are limited in number, and they are predominantly related to ethical reasons (Table 2).

**Table 2 T2:**
[figure not shown]
Exclusion criteria.

#### Intervention

1.2.2

A total of 30 patients will be treated with 2 consecutive 24 h-treatments of cytokine adsorption with the CytoSorb-device. The device will be changed after the first 24 h-treatment period. As appropriate, the CytoSorbents (CytoSorb)-cartridge will be used without additional extracorporeal devices in a hemoperfusion modality or combined with continuous veno-venous hemo (dia)filtration (CVVH (D)F). According to the manufacturer's recommendation the target blood flow is 150 (-200) mL/min. It should not fall below a limit of 120 mL/min.

Anticoagulation will be performed in analogy to renal replacement therapy and at the discretion of the treating physician. In case of heparin anticoagulation, a partial thromboplastin time (PTT) of 50 to 60 s is recommended according to the manufacturer CytoSorbents.

Since the CytoSorb-device is capable of eliminating certain antibiotics, additional dosages will be given according to the manufacturer's recommendations.^[12]^ In case of carbapenem treatment during CytoSorb treatment, an antibiotic dosage in the upper normal range without additional applications is recommended.

#### Outcomes

1.2.3

Primary and major secondary outcomes are given in Table 3.

**Table 3 T3:**
[figure not shown]
Primary and secondary endpoints.

The primary endpoint is defined as an improvement of hemodynamics with a decrease in the vasopressor dependency index (VDI) of at least 20% within 48 h compared to the baseline measurement immediately before the onset of therapy with CytoSorbents (CytoSorb). For patients without vasopressor therapy at baseline, the primary endpoint is defined as an improvement in CPI of at least 20%.

The VDI is defined as the ratio of the inotropic score divided by mean arterial pressure (MAP):

VDI = inotropic score / MAP

The inotropic score is defined as (dopamine dose_1) + (dobutamine dose∗1) + (adrenaline dose∗100) + (noradrenaline dose∗100) + (phenylephrine dose∗100). All doses are given as μg/kg/min.

TPTD will be performed at baseline as well as after 6, 8, 12, 16, 24, 30, 32, 36, and 48 h after the initiation of blood purification.

Outcome analysis will be based on a comparison of the incidence of the primary endpoint in 30 intervention patients compared to 60 matched controls with advanced hemodynamic monitoring recruited from recent studies in SAP within the same setting and the same centers. To account for different numbers of TPTD measurements in the controls (usually 2–3 measurements within 24 h), the primary outcome analysis will be performed based on the measurements at baseline as well as after 12, 24, 36, and 48 h after the initiation of CytoSorb-therapy.

APACHE-II-score on inclusion and baseline VDI are the main criteria for matching.

Secondary analyses will include laboratory (cytokine levels) and translational endpoints (including multiplex-ELISAs of numerous anti- and pro-inflammatory cytokines/chemokines and DNA analyses).

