### Statistics

1.3

The incidences of the primary endpoint and all dichotomous secondary endpoints will be compared using the Chi-Square test or Fisher exact test as appropriate.

All comparisons of continuous endpoints within groups and between groups will be performed using *t* test or Wilcoxon-test for paired or unpaired samples as appropriate.

A p-value of *P*<.05 is considered as significant.

Missing values over time will be replaced using “last value carried forward”.

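### The CPI rule for patients without a vasopressor at baseline can score a patient as a responder after a vasopressor or inotrope has been started

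*Protocol article*

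**What the plan says.** Section 1.2.3 sets two responder rules. A patient on a vasopressor at baseline responds with a "decrease in the vasopressor dependency index (VDI) of at least 20% within 48 h compared to the baseline measurement" taken immediately before CytoSorb begins. For the others, "For patients without vasopressor therapy at baseline, the primary endpoint is defined as an improvement in CPI of at least 20"%.

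The index is "VDI = inotropic score / MAP". The score has five drug terms: dopamine and dobutamine with weight 1, then "adrenaline dose∗100) + (noradrenaline dose∗100) + (phenylephrine dose∗100". No other agent has a term. The article gives no formula for CPI.

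The primary analysis uses "measurements at baseline as well as after 12, 24, 36, and 48 h after the initiation of CytoSorb-therapy". The Statistics section (1.3) says "Missing values over time will be replaced using “last value carried forward", which concerns missing values and not drug changes. The aim (1.1) is to learn whether the device "substantially improves hemodynamic characteristics including vasopressor dosage and cardiac power index (CPI").

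**The concern.** A VDI of 0 cannot fall by 20%, so patients without a vasopressor need a rule of their own. The rule chosen looks only at CPI. Vasoactive drugs act on blood pressure and cardiac output, so CPI can rise because support was started and not because the patient recovered.

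The same event then has opposite signs in the two halves of one endpoint. Starting a drug from the score makes VDI worse, yet it can turn a patient judged on CPI into a success. These patients are expected in the trial: section 1.2.4 pre-defines subgroups with and without vasopressor use at baseline, and the Discussion says that only patients at high risk of organ failure are included.

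The controls are matched, non-randomised patients from other studies, chiefly EAGLE. The rate at which such drugs are started may therefore differ between groups for reasons unrelated to the device. Unequal rates could bias the comparison, and equal rates would dilute it.

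**Working it through.** **Inputs.** From the article: the two rules, the VDI formula and the score (1.2.3); 67% of 30 against 33% of 60, power 87.8% (1.3.1); significance at P<.05 (1.3). Assumed: CPI = k × MAP × cardiac index (CI), and a two-sided test. All haemodynamic values and misclassification rates below are illustrative.

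**1. The plan's own figure.** Pooled rate = (30×0.67 + 60×0.33)/90 = 0.4433. Standard error under no difference = √(0.4433×0.5567×(1/30+1/60)) = 0.1111. Under the alternative it is √(0.67×0.33/30 + 0.33×0.67/60) = 0.1051. Power = Φ((0.34 − 1.96×0.1111)/0.1051) = 87.8%. The stated power reproduces and is not in dispute.

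**2. The CPI rule.** CPI ratio = (MAP₁ × CI₁)/(MAP₀ × CI₀). Success needs a ratio of at least 1.20 against the pre-therapy value.

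| MAP, mmHg | CI | CPI change | Scored as |
|---|---|---|---|
| 65 to 78 | constant | +20% | success |
| constant | 2.5 to 3.0 | +20% | success |
| 60 to 75 | 3.0 to 3.0 | +25% | success |
| 60 to 75 | 3.0 to 2.9 | +21% | success |
| 60 to 75 | 3.0 to 2.8 | +17% | failure |
| 60 to 75 | 3.0 to 2.5 | +4% | failure |
| 60 to 75 | 3.0 to 2.4 | 0% | failure |

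Suppose the first row follows a start of noradrenaline at dose d. VDI moves from 0 to 100d/78, which is positive for any d. The patient is worse on VDI and is counted as a success. The lower rows show that a drug start does not by itself produce success.

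**3. The VDI rule, for contrast.** Raising a listed drug counts against the patient. Noradrenaline 0.40 to 0.50 µg/kg/min at MAP 65 takes VDI from 40/65 = 0.615 to 50/65 = 0.769 (+25%). MAP would have to reach about 101.6 for this patient to score as a success. An agent outside the score leaves no trace: noradrenaline 0.30 to 0.20 at MAP 65 gives 0.462 to 0.308 (−33%), whatever made the reduction possible.

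**4. Possible size.** Let f be the share of all true failures in a group that is scored as success. Only patients without a baseline vasopressor can contribute through the CPI rule, and the article does not give their number.

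- Equal f in both groups: the rates become 0.67 + 0.33f and 0.33 + 0.67f, and the difference shrinks to 0.34(1 − f).

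| f | Rates | Power |
|---|---|---|
| 0% | 67.0% vs 33.0% | 87.8% |
| 5% | 68.7% vs 36.4% | 84.0% |
| 10% | 70.3% vs 39.7% | 79.7% |
| 20% | 73.6% vs 46.4% | 70.0% |
| 30% | 76.9% vs 53.1% | 59.6% |

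- No true effect (33% in both groups), f = 10% in treated and 0% in controls: 39.7% vs 33%, about a 9% chance of a significant result favouring the device.
- No true effect, f = 20% in treated and 0% in controls: 46.4% vs 33%, about 24%.

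Without misclassification the chance in that direction would be 2.5%. If drugs are started more often in controls, the bias runs against the device.

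**The case against.** Several objections limit the point.

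- **Reference value.** A reader might infer that a patient who goes into shock and receives a vasopressor becomes a responder. The comparison is with the pre-therapy value, not with the lowest value reached. A drug that only restores MAP and cardiac index to baseline gives a change of about 0%. False success needs a net rise of 20% above baseline. This stands, so the claim is that the rule can misclassify, not that it will.
- **Aim.** The article does not make lower vasopressor need its only aim. Section 1.1 names CPI beside vasopressor dosage. A CPI rise is therefore a legitimate target, but that does not settle how to score one that follows newly started support.
- **More drug starts, more successes.** This does not hold in general, because under the VDI rule a listed drug counts against the patient unless MAP rises proportionally more.
- **Agents outside the score.** The gap follows from the formula, but the article mentions no such agent, and the Discussion presents VDI as an index used in earlier studies. This supports a sensitivity analysis and no change to the index.
- **Fragility.** Against 20/60 controls, moving from 16/30 to 17/30 takes the uncorrected chi-square p-value from 0.068 to 0.034. Any binary endpoint of this size behaves that way, so it says nothing about this rule.
- **Unseen text.** Table 3 and the full protocol are not shown and may hold a condition. That lowers confidence. The running text nevertheless states a complete definition without one, so this is more than a detail left to another document.

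The pre-defined subgroups separate patients by baseline vasopressor use but do not change how the primary endpoint is scored.

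**Conclusion.** The point holds for the CPI rule. As stated in 1.2.3, a patient without a vasopressor at baseline can be counted as a responder after a vasopressor or inotrope is started, although VDI has gone from 0 to positive. This needs CPI to end at least 20% above its pre-therapy value, and the examples assume CPI proportional to MAP times cardiac index. VDI is 0 at baseline only if no listed inotrope is running either.

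The size is unknown, because the article gives neither the share of patients judged on CPI nor how often drugs are started. The figures of 79.7% power and 24% false positives rest on assumed rates and show only what would follow from them. Equal rates would cost power, and unequal rates could bias the result in either direction. The documents do not show that the comparison will point the wrong way. Confidence is moderate, since a condition in Table 3 cannot be excluded.

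**What to change.** The change concerns scoring only, not treatment.

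- **Primary endpoint.** For patients without a vasopressor at baseline, define response as a CPI rise of at least 20% with no vasopressor or inotrope started between baseline and the assessment. Score any such start as non-response, by the same rule in cases and controls. State the CPI formula. If Table 3 already contains such a condition, repeat it in the text of 1.2.3.
- **Sensitivity analysis only.** Where the control records allow it, score the start of a vasoactive agent outside the five-drug score as non-response under the VDI rule. Leave the index itself unchanged.

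The text cost is a few sentences, to be settled before outcome analysis. Response rates would be somewhat lower in both groups, so the assumed 67% and 33% should be looked at again. The rule also needs drug-start data in the control records. The article does not say that these were kept, so this should be checked first.

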With regard to the complexity of numerous diagnostic and therapeutic approaches in SAP, the impact of single measures such as 2-day extracorporeal cytokine elimination should not be overestimated. Necessarily, this has to be considered for the study design, in particular for the primary endpoint and the power calculation. Therefore, we chose changes in the VDI as the primary endpoint. VDI has been repeatedly used as an endpoint in studies focused on extracorporeal cytokine and toxin elimination.^[12,18]^

Patients similar to the patients selected according to the inclusion criteria of PACIFIC have been treated by most PACIFIC study centers during the randomized controlled EAGLE-trial (https://clinicaltrials.gov/ct2/show/NCT00894907). The EAGLE-study investigates the impact of TPTD guided volume resuscitation on outcome. Half of the intended number of 182 patients of the EAGLE-study will be under hemodynamic monitoring with the PiCCO-device. Since the inclusion criteria and the clinical setting are nearly identical as for PACIFIC, data from patients from the EAGLE-study with PiCCO-monitoring will be a major source for the allocation of matched controls.

In addition to the primary endpoint and several standard secondary outcomes such as organ failures and mortality, the PACIFIC-trial will analyze several measures of inflammation at baseline and over time. The importance of pro-inflammatory cytokines in pancreatitis has been highlighted by a recent study in 84 patients with AP who were screened for known polymorphisms in TNFα, interleukin 1 (IL-1), IL-1 receptor antagonist (IL1RN), IL-6, and IL-10. The study demonstrated that the TNFα −238 AG genotype, but not the TNFα −308 SNP, was associated with organ failure (shock and/or respiratory failure) during AP.^[19,20]^ A very interesting candidate that seems to drive the pathophysiology of MOF during AP in experimental animal models is IL-6. IL-6 not only regulates the acute phase response in the liver, it can also activate a plethora of pro-inflammatory pathways, such as Stat3 and NF-kappaB.^[21]^

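### Baseline and the 48 h clock are set only by CytoSorb start, which controls never have, and time since pain onset is not named for matching, so spontaneous change can pass for a device effect in either direction

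*Protocol article*

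**What the plan says.** Section 1.2.3 of the protocol article defines the primary endpoint as a fall in VDI of at least 20% (or, without vasopressors at baseline, a 20% improvement in CPI) "within 48 h compared to the baseline measurement immediately before the onset of therapy with CytoSorbents (CytoSorb"). Because controls have fewer thermodilution measurements, the primary analysis is restricted to "baseline as well as after 12, 24, 36, and 48 h after the initiation of CytoSorb-therapy".

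The same endpoint is compared between 30 treated patients and 60 matched controls. Section 1.1 says that controls come from a comparable setting with TPTD monitoring, "but not treatment with CytoSorb or any other cytokine adsorbing devices". On matching, section 1.2.3 says: "APACHE-II-score on inclusion and baseline VDI are the main criteria for matching".

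On disease time, section 1.2.1 says: "Inclusion is limited to a maximum of 7 days after the onset of pain", and adds: "This period is considered as the early phase of SAP, including the first peak of inflammation due to a SIRS". The Discussion says that "data from patients from the EAGLE-study with PiCCO-monitoring will be a major source for the allocation of matched controls", and gives the reason: "Since the inclusion criteria and the clinical setting are nearly identical as for PACIFIC".

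Section 1.3 tests the primary endpoint with a chi-square or Fisher exact test, without adjustment.

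**The concern.** The endpoint is a change from a time zero, and that time zero is an event that two-thirds of the analysed patients cannot have. The sentence that adapts the schedule to the controls still counts hours from CytoSorb start.

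The matching inherits the gap. A control's baseline VDI is undefined until the control's baseline is defined. APACHE-II is taken at inclusion, which need not be the moment at which CytoSorb starts. Matching on the level of VDI does not match on its direction: two patients with the same VDI, one before the inflammatory peak and one after it, would count as equivalent, although their next 48 h may differ without any treatment.

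At stake is the meaning of the primary comparison. If cases and controls sit at different points of the disease course, their response rates can differ with no device effect, and the unadjusted test does not correct for this.

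**Working it through.** **1. The plan's own figure.** Section 1.3.1 gives 67% of 30 versus 33% of 60 and a power of 87.8%. Section 1.3 gives P<.05; two-sided is assumed.
- Pooled proportion: (30×0.67 + 60×0.33)/90 = 39.9/90 = 0.4433
- SE under the null: √[0.4433×0.5567×(1/30+1/60)] = 0.1111
- SE under the alternative: √[0.67×0.33/30 + 0.33×0.67/60] = 0.1051
- z = (0.34 − 1.96×0.1111)/0.1051 = 1.163, so power = Φ(1.163) = 87.8%

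The arithmetic is right. It treats the whole 34-point gap as a device effect.

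**2. What fixes time zero in each group.**

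| Element | Treated | Controls |
|---|---|---|
| Baseline | Immediately before CytoSorb start | Not stated |
| 12, 24, 36, 48 h | From CytoSorb start | Not stated |
| APACHE-II | At inclusion | At inclusion (which inclusion is not stated) |
| Time from pain onset | At most 7 days at inclusion | Bounded only through similar entry criteria |
| Adjustment in the test | None | None |

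Within the window, a case and its control could differ by up to about 7 days.

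**3. Effect of a shift in responders.** Assumptions not in the documents: CytoSorb has no effect, the control rate is 33% (the planning value), and misaligned time zero raises the treated group's rate by b points. All 30/60 binomial outcomes were enumerated for the uncorrected two-sided chi-square test at 5%.

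| b | Treated vs control | Significant, either direction | Significant in favour of CytoSorb | In favour, Fisher |
|---|---|---|---|---|
| 0 | 33% vs 33% | 5.0% | 2.7% | 1.9% |
| 5 | 38% vs 33% | 8.0% | 7.3% | 5.6% |
| 10 | 43% vs 33% | 16.2% | 16.0% | 13.0% |
| 20 | 53% vs 33% | 46.1% | 46.0% | 41.4% |

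**4. From a spontaneous fall in VDI to a shift in responders.** This uses an assumed model: log-VDI is a stationary AR(1) process, response is a 20% fall at any of 12, 24, 36 or 48 h, controls have no drift and treated patients drift down. A drift of −0.025 per 12 h gives e^(−0.10) = 0.905, a fall of about 10% over 48 h; −0.05 gives e^(−0.20) = 0.819, about 18%.

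With SD 0.3 and 12 h autocorrelation 0.8:
- no drift: 39% respond
- 10% fall: 49% respond; test significant in about 16% of trials
- 18% fall: 60% respond; test significant in about 47–48%

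Over SD 0.2–0.5 and autocorrelation 0.6–0.9, the test is significant in about 7–45% of trials for the 10% fall and about 13–97% for the 18% fall. A 5% fall at SD 0.3 and autocorrelation 0.8 gives 44% versus 39% and about 8%. The model covers VDI only, not the CPI version of the endpoint, and does not include matching on baseline VDI.

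**The case against.** The strongest reply is that this is a condensed article. The matching criteria are called the main ones, which leaves room for others. A full protocol or SAP may define a control index time, and Tables 1–4 are not shown. A parallel control baseline is evidently intended, since the measurement grid was thinned to suit the controls. Disease time is also limited: entry closes at 7 days, the main control source has closely similar entry criteria, and setting and centres are shared.

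Much of this stands. It is not supportable to say that time since pain onset is left unmatched, only that it is not named. A reader might also infer that controls will be timed from inclusion in their own trial, that VDI rises on early days and falls on later ones, or that the bias must favour CytoSorb. The document says none of these. It gives no VDI by disease day, and if control baselines fall later in the course, the bias can run against the device. Nor is the 47–48% figure an expected error rate: it requires every treated patient to drift down by 18% while every control stays flat, under assumed variability.

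What does not fall away is that the text fixing the primary comparison counts from CytoSorb start for both groups, and the matching rule as stated can pair patients in different phases of the disease. Similar entry criteria bound the difference within a window that itself contains the peak; they do not align time zero inside it.

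**Conclusion.** The point holds in a limited form. As written, the primary endpoint has no time zero for controls, and the named matching criteria do not align disease time. Spontaneous change can therefore be read as a device effect in either direction.

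Neither size nor sign follows from the document. As an illustration, a modest shift of 10 points in responders roughly triples the nominal 5% error rate, to about 16%, and 20 points takes it to about 46%. The spontaneous falls that would produce such shifts depend heavily on the assumed variability, which is why the model ranges are so wide. The stated power is correctly computed and is not in question.

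**What to change.** State a control index time: the TPTD measurement nearest to the matched case's elapsed time from pain onset at CytoSorb start. Choose only controls who are alive, TPTD-monitored and meet PACIFIC criteria at that time. In both groups, take baseline VDI at that time (and APACHE-II where available) and read the 12, 24, 36 and 48 h assessments from it. Add time from pain onset to the matching criteria. Settle this before controls are selected.

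Keep the planned chi-square or Fisher test as primary, since the plan has no primary model to which a term could be added, and add a sensitivity analysis adjusted for time since onset.

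The cost is wording plus a matching rule. The downside is fewer eligible controls per case, so some sets may be looser on APACHE-II or VDI, or smaller than 1:2. The rule also requires that onset time is recorded for controls, which the article does not say and which should be checked first.
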